**Fig. 3 Fig3:**
[figure not shown]
Images demonstrating the satisfactory imaging for IA-SCB (**A**, **B**) and the double-injection (**C**) and triple-injection (**D**) techniques used in IA-SCB. **A**, **B** The satisfactory imaging of the individual trunks of the brachial plexus in the supraclavicular fossa. **C** Sites of injection in the DI method: the needle tip (dotted arrows) is orientated to the intertruncal planes of the 3 trunks (first injection in the lower intertruncal plane, second in the upper plane), and the desired spread pattern of LA will be confirmed by ultrasound. **D** Sites of injection in the TI method: the needle tip (dotted arrows) is orientated orderly to the outer boundaries (epineurium) of the trunks, and the desired spread pattern of LA will be confirmed by ultrasound. The injection sequence is from bottom to top, that is the first injection for the lower trunk, second for the middle trunk, and last for the upper trunk. A, anterior division of upper trunk; p, posterior division of upper trunk; SSn, suprascapular nerve; L, lower trunk; M, middle trunk; Pl, pleura; R1, first rib; SA, subclavian artery; dotted line = intertruncal planes; ASM, anterior scalene muscle; LA, local anesthetics; IA, intertruncal approach; SCB, supraclavicular block; DI, double injection; TI, triple injection

### Outcome measures

#### Primary outcome measure

The primary outcome will be the percentage of patients with complete sensory blockade of all 4 terminal nerves (median, ulnar, radial, and musculocutaneous nerves) of the brachial plexus measured at 20 min after injection. The sensory blockade will be evaluated using a validated 3-point scale (0 = no block, the patient has normal sensation; 1 = partial anesthesia, the sensation is reduced compared with the contralateral limb; and 2 = complete anesthesia) by an outcome evaluator (either anesthesiologist or anesthesia nurse). Sensory blockade of the musculocutaneous, median, radial, and ulnar nerves will be evaluated on the lateral aspect of the forearm, the volar aspect of the thumb, the lateral aspect of the dorsum of the hand, and the volar aspect of the fifth finger, respectively. The complete sensory for each innervated nerve was defined as score is equal to 2 points. We will consider the patients having a complete sensory blockade when a minimal composite score of 7 points is achieved.

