**Methods:**

This study is a prospective parallel-group randomized controlled trial. A total of 86 end-stage renal disease patients will be randomly allocated to receive IA-SCB using either DI or TI technique with identical LA (0.5% ropivacaine 24 mL). The primary outcome is the percentage of patients with complete sensory blockade of all 4 terminal nerves (median, ulnar, radial, and musculocutaneous nerves) of the brachial plexus measured at 20 min after injection. The secondary outcomes will consist of the sensory or motor blockade of all individual nerves, onset times, performance time, diaphragmatic paralysis, surgical anesthesia, and adverse events.

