#### Secondary outcome measures

The onset time is defined as when a minimal composite sensory-motor score of 14 points is achieved. The assessment of sensory-motor blockade will be performed every 5 min until 30 min after injection. The above 3-point scale is used for evaluating sensory blockade, and another similar 3-point scale (0 = no block, 1 = paresis, 2 = paralysis) for motor blockade. Motor blockade of the musculocutaneous, radial, median, and ulnar nerves will be evaluated by elbow flexion, thumb abduction, thumb opposition, and thumb adduction, respectively.The performance time (including imaging time and needle time) is defined as the time interval between contact of the ultrasound probe with the skin and complete injection of LA.The incidence of diaphragmatic paralysis measured with M-mode as described by Boussuges et al. [13] at 35 min after injection.Successful surgical anesthesia is defined as one with adequate surgical block without complaining pain during simulated surgical stimulus (forceps pinching the prospective surgical area) at 30 min after injection.Operation-related adverse events include puncture-related paresthesia, procedural-related pain, Horner syndrome, vascular puncture, pneumothorax, toxicity of LA, or neurological deficits. The puncture-related paresthesia will be recorded by self-report during performing nerve block, and the procedural-related pain is assessed by the numeric rating scale (0 = no pain, 10 = worst possible pain). Horner syndrome, vascular puncture, pneumothorax, and toxicity of LA will be recorded as the incidence in each group. All patients will be followed up for 72 h after surgery for suspicious symptoms of nerve injury such as paresthesia or motor deficit.

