### Sample size calculation

Sample size is calculated according to the study of Arab and colleagues [7]. In clinical practice, multipoint injection and satisfactory diffusion of LA will result in more complete sensory or motor blockade and faster onset times. Therefore, we expected a higher rate of complete sensory blockade using the new TI technique. Based on a pilot study (15 patients), the rate was 66.7% (patients with complete sensory blockade) at 20 min after injection, when patients received a standardized IA-SCB with the DI technique. We hypothesized that the TI technique will be capable of increasing this rate to 90%; with a statistical power of 0.80 and a *α* level of 0.05, the required sample size is calculated to 36 patients per group. A total of 43 patients per group will be required to account non-included patients (15% dropout rate).

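### The primary endpoint is worded as complete block of all four nerves (8 of 8 points), but the responder rule accepts 7, which always leaves one nerve partial

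*Protocol article*

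**What the plan says.** Under Primary outcome measure, the protocol article makes the endpoint a responder proportion, where the response is "complete sensory blockade of all 4 terminal nerves (median, ulnar, radial, and musculocutaneous nerves) of the brachial plexus measured at 20 min after injection". Each nerve is scored 0, 1 or 2, with "1 = partial anesthesia, the sensation is reduced compared with the contralateral limb; and 2 = complete anesthesia". The per-nerve definition follows: "The complete sensory for each innervated nerve was defined as score is equal to 2 points". The patient-level rule comes next: "We will consider the patients having a complete sensory blockade when a minimal composite score of 7 points is achieved".

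The Methods part of the abstract repeats the four-nerve wording with no threshold: "The primary outcome is the percentage of patients with complete sensory blockade of all 4 terminal nerves".

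Sample size calculation takes its control rate from a 15-patient pilot of the double-injection technique: "the rate was 66.7% (patients with complete sensory blockade) at 20 min after injection". The triple-injection technique is hypothesised to raise this to 90%. Neither figure comes with a scoring rule.

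**The concern.** The outcome and the rule that decides who meets it differ by one point, and that point separates a complete block from a partial one on the protocol's own scale. Under the rule, the trial would report complete blockade of all four nerves for some patients who do not have it.

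This bears on the question the trial asks. The Introduction names incomplete block in the ulnar territory as a weakness of existing supraclavicular techniques, and the Discussion gives reliable block of all four nerves as a reason for trying triple injection. A patient with three complete nerves and a partial ulnar block is a failure under the outcome as worded and a success under the rule.

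The planning rates inherit the ambiguity. If they were obtained under one rule and the trial is analysed under the other, the planned power does not apply.

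**Working it through.** **1. The plan's own sample size.** Inputs from Sample size calculation: 66.7% vs 90%, power 0.80, alpha 0.05, 36 per group, then 43 after 15% dropout. With unpooled variance, n = (z_alpha + z_beta)² × [p1(1−p1) + p2(1−p2)] / (p1−p2)².
- Variance term: 0.667×0.333 + 0.90×0.10 = 0.3121. Squared difference: 0.233² = 0.0543.
- One-sided: (1.645 + 0.842)² × 0.3121 / 0.0543 = 35.5, so 36. This matches.
- Two-sided: (1.960 + 0.842)² × 0.3121 / 0.0543 = 45.1, so 46. This does not match.
- Dropout: 36 / 0.85 = 42.4, so 43. This matches.

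The stated figure thus reproduces with a one-sided calculation only. That is a separate matter; the powers below are two-sided.

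**2. The two definitions.** Four nerves at 2 points give 4 × 2 = 8, the maximum. Of the 3⁴ = 81 possible score patterns, one meets the outcome as worded: (2,2,2,2). Five meet the rule of at least 7: that one, plus the four patterns with three nerves at 2 and one at 1. No patient with a nerve at 0 can reach 7, since the other three give at most 6. The two definitions therefore disagree only for patients scoring exactly 7, and every such patient has exactly one partial nerve.

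**3. What the gap could do to the rates and power.** The share scoring exactly 7 is not given, so this step is illustrative. Assume that each incomplete nerve scores 1 and that each nerve is complete with probability p.
- Independent nerves: P(8) = p⁴ and P(≥7) = p⁴ + 4p³(1−p).
- Within-patient correlation ρ: the number of complete nerves is beta-binomial with parameters p(1/ρ−1) and (1−p)(1/ρ−1).

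Solve p to match 66.7% and 90% under one rule, then read off the rates under the other. Example with independence: P(≥7) = 0.667 gives p = 0.709 and P(8) = 0.252; P(≥7) = 0.90 gives p = 0.857 and P(8) = 0.541. Power is for the two-sided chi-square test by full enumeration, 43 per group, no losses. For 66.7% vs 90% it is 78%.

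| ρ | Planning rates are ≥7 rates; 8/8 analysed | Power | Planning rates are 8/8 rates; ≥7 analysed | Power |
|---|---|---|---|---|
| 0 | 25.2% vs 54.1% | 81% | 95.1% vs 99.6% | 13% |
| 0.4 | 46.9% vs 79.9% | 91% | 81.9% vs 95.3% | 55% |
| 0.8 | 60.7% vs 87.5% | 84% | 72.2% vs 92.1% | 71% |

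**4. Sensitivity to the model.** Step 3 gives both arms the same correlation. Instead, take the planning rates as ≥7 rates and simply subtract an assumed share scoring exactly 7 in each arm (double / triple injection). By normal approximation, which gives 76% for the planned rates at 43 per group:
- 5% / 5%: 61.7% vs 85%, power 69%.
- 10% / 10%: 56.7% vs 80%, power 65%.
- 20% / 5%: 46.7% vs 85%, power 97%.
- 5% / 10%: 61.7% vs 80%, power 46%.

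The effect can go either way even when the direction of the mismatch is fixed.

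**The case against.** The strongest defence is that the protocol does give one explicit patient-level rule. The per-nerve definition may serve the secondary outcomes on individual nerves, and an analyst following the text would compute the rate of 7 or more. The onset threshold, 14 of 16, is the same fraction as 7 of 8, which suggests a deliberate tolerance. The pilot rate is described in nearly the words that the rule defines, so it was probably scored at 7 or more. All of this is fair, and it means that 8 of 8 cannot be presumed to be the intended rule. It does not remove the conflict: the outcome is still worded as complete block of all four nerves, and no section justifies or explains the cut-off of 7.

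Three stronger readings are tempting and should not be drawn.
- A reader might infer that power collapses to about 13%. That is the lowest cell of the table. It needs a pilot scored at 8 of 8, which no section says, and independence between nerves blocked by the same injections in one patient, which is implausible.
- A reader might count the onset rule ("The onset time is defined as when a minimal composite sensory-motor score of 14 points is achieved") as a further contradiction, since 8 motor and 6 sensory points reach 14 in a patient who fails the primary endpoint. Onset is a separate sensory-motor composite and need not imply the sensory endpoint.
- A reader might think that the title or closing conclusion overclaims. Both speak of block dynamics in general and do not use the four-nerve wording.

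**Conclusion.** The point stands as an internal contradiction in the primary endpoint. It rests on the protocol's own scale and on 4 × 2 = 8, and on no assumption. Applied as written, the rule would label patients with one partial nerve as complete in all four.

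The numerical consequence is not known. In the correlation model, with ρ from 0 to 0.8, power at 43 per group is about 81% to 91% if the planning rates are ≥7 rates and 8/8 is analysed. It is about 13% to 71% if they are 8/8 rates and ≥7 is analysed. The first pairing starts from the reading closest to the text, but its favourable range belongs to that model; equal shares scoring exactly 7 in both arms would lower power instead. The documents do not show which threshold was intended.

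**What to change.** Before unblinding, reconcile the passages so that one responder rule governs the primary outcome, the pilot rate and the 90% target. Either of these would do:
- define the outcome as a score of 2 in each of the four nerves at 20 minutes (8/8); or
- keep the threshold of 7 and describe the outcome as a composite sensory score of at least 7 of 8, without calling it complete blockade of all four nerves, in the abstract as well as under Primary outcome measure.

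Report the other threshold as a pre-specified sensitivity analysis. Confirm which rule gave the pilot result (66.7% of 15 is 10 patients). If it differs from the rule adopted, re-derive the sample size inputs.

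No new data are needed, because both versions come from the four nerve scores already collected. The cost is procedural. Trial status says that patients had already taken part, and Protocol amendments allows changes in principle only for safety, so the correction needs a documented amendment with ethics approval and a stated reason. Settling it before outcomes are seen by group keeps the choice from being data-driven. If 8/8 is adopted, response rates cannot be higher than under ≥7 and will be lower wherever patients score exactly 7.

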#### Secondary outcome measures

The onset time is defined as when a minimal composite sensory-motor score of 14 points is achieved. The assessment of sensory-motor blockade will be performed every 5 min until 30 min after injection. The above 3-point scale is used for evaluating sensory blockade, and another similar 3-point scale (0 = no block, 1 = paresis, 2 = paralysis) for motor blockade. Motor blockade of the musculocutaneous, radial, median, and ulnar nerves will be evaluated by elbow flexion, thumb abduction, thumb opposition, and thumb adduction, respectively.The performance time (including imaging time and needle time) is defined as the time interval between contact of the ultrasound probe with the skin and complete injection of LA.The incidence of diaphragmatic paralysis measured with M-mode as described by Boussuges et al. [13] at 35 min after injection.Successful surgical anesthesia is defined as one with adequate surgical block without complaining pain during simulated surgical stimulus (forceps pinching the prospective surgical area) at 30 min after injection.Operation-related adverse events include puncture-related paresthesia, procedural-related pain, Horner syndrome, vascular puncture, pneumothorax, toxicity of LA, or neurological deficits. The puncture-related paresthesia will be recorded by self-report during performing nerve block, and the procedural-related pain is assessed by the numeric rating scale (0 = no pain, 10 = worst possible pain). Horner syndrome, vascular puncture, pneumothorax, and toxicity of LA will be recorded as the incidence in each group. All patients will be followed up for 72 h after surgery for suspicious symptoms of nerve injury such as paresthesia or motor deficit.

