### Statistical plan

Statistical analysis will be performed using SPSS version 20 statistical software (SPSS Inc, Chicago, IL). Firstly, an overall descriptive analysis and inferential statistics for all clinical variables in both groups will be performed. Numbers and percentages will be recorded for categorical variables, and mean (SD) and interquartile intervals for continuous variables. For all data, normal distribution will be examined by the Kolmogorov-Smirnov test. The basic information (such as age, BMI, and performance times, etc.) will be analyzed using chi-square tests or Fisher’s exact test or independent *t* test as appropriate. The percentage of patients with a complete sensory blockade at all predetermined time points and onset times will be analyzed using the Mann-Whitney *U* test or independent *t* test. The incidence of diaphragmatic paralysis, surgical anesthesia, and operation-related adverse events will be analyzed using chi-square tests or Fisher’s exact test. A *P* value inferior to 0.05 will be considered statistically significant for all results.

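### Onset time is right-censored at 30 min, but the planned t test, Mann-Whitney test and mean (SD) have no value for a patient who has not reached 14 points by then

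*Protocol article*

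**What the plan says.** Under Secondary outcome measures, the protocol article defines the endpoint: "The onset time is defined as when a minimal composite sensory-motor score of 14 points is achieved". It then fixes the observation window: "The assessment of sensory-motor blockade will be performed every 5 min until 30 min after injection". Four nerves are scored 0 to 2 for sensation and 0 to 2 for motor function, so the maximum is 16.

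The Statistical plan says that "onset times will be analyzed using the Mann-Whitney" U test or an independent t test. Its general rule for summaries is "mean (SD) and interquartile intervals for continuous variables". A normality check is planned. The article names no time-to-event method and gives no value, rank or censoring rule for a patient who is below 14 at the last assessment.

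The Sample size calculation supplies the only expected rates, and these are for sensory block alone at 20 min: "Based on a pilot study (15 patients), the rate was 66.7% (patients with complete sensory blockade) at 20 min after injection" with double injection (DI), and for triple injection (TI) "We hypothesized that the TI technique will be capable of increasing this rate to 90"%.

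**The concern.** The endpoint is a time to an event, observed only up to 30 min. For a patient who has not reached 14 by then, all that is known is that onset exceeds 30 min. A t test and a mean need a number for every patient, and Mann-Whitney needs at least a rank. With neither defined, software leaves the patient out. The comparison is then made among those whose block succeeded, a group formed after randomisation.

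The trial itself expects the two arms to differ in how many blocks are complete. Excluding non-achievers would then remove the slowest patients mainly from the slower arm. That shrinks the onset difference and costs power. If the techniques differed only in how many patients reach the threshold, the onset analysis would show nothing. With no rule stated, the handling could also be chosen after the data are seen. The Discussion treats onset time as part of the block dynamic that the trial sets out to assess, so the result will be read closely.

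**Working it through.** **The plan's own figures.** The article gives no figure for onset time, so there is none to reproduce. From the Sample size calculation I take 36 evaluable patients per arm; 36 / (1 − 0.15) = 42.4, rounded up to the stated 43. How the 36 was reached is a separate matter.

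**Can patients fail to reach 14?** The maximum is 4 nerves × 2 points × 2 modalities = 16. Even with full sensory block (8 points), a score of 14 needs 14 − 8 = 6 of the 8 motor points. The planning rates leave 100 − 66.7 = 33.3% of DI and 100 − 90 = 10% of TI patients without complete sensory block at 20 min. Some patients below 14 at 30 min are therefore plausible, with more in DI. The share is not in the document and has to be assumed.

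**Main illustration.** Assume Weibull onset with shape k, calibrated so that 66.7% (DI) and 90% (TI) have reached the threshold by 20 min. This borrows a sensory rate for a sensory-motor endpoint, so it is an assumption. Attainment by 30 min is then 1 − (1 − p)^(1.5^k), where 1.5 = 30/20.

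| Shape k | Exponent 1.5^k | DI by 30 min | TI by 30 min | Expected without onset, of 36 (DI vs TI) |
|---|---|---|---|---|
| 1 (exponential) | 1.5 | 1 − 0.333^1.5 = 81% | 1 − 0.10^1.5 = 97% | 6.9 vs 1.1 |
| 2 | 2.25 | 92% | 99% | 3.0 vs 0.2 |
| 3 | 3.375 | 97.6% | 99.96% | 0.9 vs 0.01 |

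Onset times were simulated, rounded up to the 5-min grid, and tested by Mann-Whitney in two ways: non-achievers dropped, or all given one common rank beyond 30 min.

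- Shape 1, 36 per arm: power about 0.38 dropped vs 0.74 ranked last. The mean difference is 3.2 min among achievers vs 5.7 min on means restricted to 30 min.
- Shape 3, 36 per arm: power about 0.69 vs 0.74. The mean difference is 3.4 vs 3.7 min.
- Shape 2 lies between; at 43 per arm (no dropout) two runs gave 0.61 and 0.65 dropped vs 0.81 ranked last.

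**Second model.** Lognormal onset (log-SD 0.3 to 0.5), 36 per arm, with attainment by 30 min set directly:

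| DI vs TI reaching 14 by 30 min | Power, dropped | Power, ranked last |
|---|---|---|
| 66.7% vs 90% | about 0.60 | 0.92–0.93 |
| 80% vs 95% | 0.69 | 0.89 |
| 97% vs 99% | 0.37 | 0.41 |
| 90% vs 90% (identical arms) | 0.04–0.05 | 0.05 |

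The last row is the rejection rate with no true difference; neither approach inflates it.

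**Limiting case.** If achievers are equally fast in both arms and only attainment differs (80% vs 95%, 36 per arm), power is 0.05 dropped and 0.20 ranked last. Dropping leaves only the false-positive rate.

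**The case against.** **No exclusion is stated.** A reader might infer that the plan drops the slowest blocks. The article does not say so. Mann-Whitney is one of the two named tests, and giving non-achievers a common worst rank within it would be sound and compatible with the wording. It can be argued that this is a coding rule that an article leaves to a fuller document. That part stands, and it limits the claim to what happens by default. It does not rescue the t test or the mean (SD), which the article itself names and which need a number that these patients do not have.

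**The size is unknown.** The 66.7% comes from 15 pilot patients and is a sensory rate at 20 min, not attainment of 14 of 16 by 30 min. The exponential case is the most unfavourable of the three shapes; at shape 3 fewer than one DI patient in 36 lacks a value and little is lost. This stands in full, so only a range can be given.

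**The 5-min grid.** A reader might infer that the t test is unsuitable because onset can take only six values. The simulations do not support that: at 43 per arm, on the same data with non-achievers dropped, the t test had slightly more power than Mann-Whitney (0.47 vs 0.45, 0.66 vs 0.61, 0.79 vs 0.77 for shapes 1 to 3). The objection to the t test is the missing value alone.

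**Consequences are limited.** Onset is secondary, the bias runs towards no difference, and failed blocks also appear in complete sensory block at each time point and in surgical anesthesia at 30 min. All true, although neither of those is the 14-point sensory-motor endpoint.

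**Conclusion.** The concern holds as a mismatch between a stated endpoint and its stated analysis. Onset time is censored at 30 min, and the named methods have no value for a patient who has not reached 14 points. If such patients are left out, and they are commoner with DI, the onset difference is understated and power falls.

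Under the assumed calibration to 66.7% vs 90% at 20 min, with 36 evaluable per arm, Mann-Whitney power with non-achievers dropped vs ranked last ranges from about 0.38 vs 0.74 (81% vs 97% attain by 30 min) to 0.69 vs 0.74 (98% vs nearly 100% attain). The loss is negligible if almost everyone attains, and there is no bias if the arms are identical. The existence of the gap is certain; its size is not.

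A reader might infer that the trial's main conclusion is at risk, or that a false advantage for TI could arise. Neither follows: the primary outcome is a percentage at 20 min and is untouched, and when DI has more non-achievers the bias works against TI. The point is worth correcting but is not critical.

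**What to change.** Pre-specify one analysis of onset time that includes every randomised patient with a block assessment: Mann-Whitney, with all patients below 14 at 30 min given a single common worst rank (beyond 30 min). Report medians, and the number in each arm not reaching 14 by 30 min.

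Kaplan-Meier curves with a log-rank test, censored at 30 min, are an acceptable alternative. The two are not equivalent: with common censoring at 30 min, the worst-rank test corresponds to a Gehan-Wilcoxon test and gives more weight to early differences, so they can give different results. Name one in advance.

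Remove the independent t test and mean (SD) for onset time. Imputing 30 or 35 min to keep them would be arbitrary and would distort the mean.

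The cost is a sentence or two in the Statistical plan. No new data or visits are needed, and the planned software can run either analysis. As patients had already been enrolled when the article was submitted, the rule should be fixed and dated before outcome data are compared by arm.

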### Inclusion criteria

Having signed the written informed consentAmerican Society of Anesthesiologists (ASA) physical status < IVAged 18–75 yearsPatients scheduled for creation or superficialization of arteriovenous fistula or aneurysmectomy or arteriovenous fistula with artificial vessels for renal dialysis

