Although our study has many similarities to Arab’s study [7], some important differences are worth noting: (1) The TI is not an intracluster-injection technique, rather than a precise sub-epineurium injection technique (puncture the epineurium of the trunks under real-time ultrasound guidance); (2) compared with the classical approach to supraclavicular block, the new intertruncal approach provides clearer anatomical details, including the 3 trunks and its hyperechoic epineurium layers, which may guide the needle tip to the targeted location without intraneural injection. Furthermore, small nerves arise from the fascicles, and the intracluster-injection technique may result in sub-perineurium injections. The TI technique deposits the LA away from the trunks, even if the needle is advanced within the neurovascular sheath. Therefore, the greatest advantage of this TI technique is that keeping the needle tip outside of the perineurium as far as possible on ultrasound imaging. We also observe the puncture-related variables (paresthesia and procedural-related pain), diaphragmatic paralysis, and neurological deficits to evaluating the safety of this TI technique. Therefore, ultrasound-guided IA-SCB with the TI technique has the potential to be as “all for one” technique of the whole upper extremity similar as selective trunk block [19, 20], which can provide more complete blockade and rapid onset time with low incidence of adverse events.

This study protocol has several limitations. First, this is a single-center study and has all the limitations inherent in that study design. Second, our study will focus on the block dynamic in patients undergoing a same type of surgery, which is insufficient statistical power for rare but serious complications. The prospective or retrospective clinical study with a large sample will be desired in the future for the incidence of nerve injury and pneumothorax. Third, we cannot completely rule out that the skill level of the operators affects the block dynamic and puncture-related complications, even if we chose all experienced ones in this study protocol.

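### Successful surgical anaesthesia is settled by a forceps pinch 30 min after injection, so a block that later proves inadequate in surgery is either kept as a success or dropped, and never scored as a failure

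*Protocol article*

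**What the plan says.** The section Secondary outcome measures gives a closed definition: "Successful surgical anesthesia is defined as one with adequate surgical block without complaining pain during simulated surgical stimulus (forceps pinching the prospective surgical area". The time point follows directly: "forceps pinching the prospective surgical area) at 30 min after injection". The article states no time of incision. That the test comes before it is inferred from the stimulus being simulated and the surgical area being prospective.

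The abstract gives the outcome its rank: "The secondary outcomes will consist of the sensory or motor blockade of all individual nerves, onset times, performance time, diaphragmatic paralysis, surgical anesthesia, and adverse" (the quote stops one word short of the end of the sentence). The Statistical plan compares it between arms as a simple incidence: "The incidence of diaphragmatic paralysis, surgical anesthesia, and operation-related adverse events will be analyzed using chi-square tests", with Fisher's exact test as the alternative.

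Two other sections bear on it. The Inclusion criteria define the population by the operation to be performed: "creation or superficialization of arteriovenous fistula or aneurysmectomy or arteriovenous fistula with artificial vessels for renal dialysis". The Dropout criteria list a switch of operation or of anaesthetic method, whether it happens ahead of surgery or in the course of it.

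**The concern.** The label promises more than the test measures. Every patient goes on to have an operation, and this is the only listed efficacy outcome that examines the surgical area; the primary outcome is scored at sites on the forearm, hand and fingers. Yet observation for it ends before the operation starts. Nothing in the primary or secondary outcomes records pain at or after incision, supplementary anaesthesia, or conversion.

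Two things are at stake. First, a result on this outcome may be reported as adequacy for arteriovenous access surgery when it shows readiness at 30 min. Second, the clearest failures, those that force a change of anaesthetic method, are handled by the dropout list. Removing them is an exclusion after randomization for a reason related to the quality of the block, which is what the two techniques are meant to differ in. If the arms differ in intraoperative failure, neither route lets the difference show.

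**Working it through.** The plan gives no figure to reproduce here. The check is to follow a patient through the sections, then to illustrate the size.

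**Step 1: what happens to a block that passes the pinch and then fails.**

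- *Method unchanged* (pain tolerated or supplemented). The Secondary outcome measures section has already scored a success at 30 min, and nothing later revises it. The patient remains a success.
- *Method changed during surgery.* The patient meets a dropout criterion. The sample-size section supports reading this as removal from the evaluable set: "A total of 43 patients per group will be required to account non-included patients (15% dropout rate"), where 36 / (1 − 0.15) = 42.4, rounded up to 43, so dropouts are treated as lost from the 36 needed. The article does not say outright how dropouts enter the analysis.

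No route leads to a recorded failure.

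**Step 2: illustration. All inputs are assumptions;** the documents give neither a pinch-pass rate nor an intraoperative failure rate. Let P be the share passing the pinch and f the share of passers whose block fails in surgery.

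- Reported rate if all failures are retained: P
- Reported rate if all failures are dropped: P(1 − f) / [P(1 − f) + (1 − P)]
- Success through the operation: P(1 − f)

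With P = 95%:

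| f | Retained | Dropped | Through surgery |
|---|---|---|---|
| 0% | 95.0% | 95.0% | 95.0% |
| 5% | 95.0% | 0.9025 / 0.9525 = 94.8% | 90.3% |
| 10% | 95.0% | 0.855 / 0.905 = 94.5% | 85.5% |
| 20% | 95.0% | 0.76 / 0.81 = 93.8% | 76.0% |

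The pattern does not hinge on P. With P = 90% and f = 5% to 20%, success through surgery is 85.5% to 72.0%, while the rate after dropping is 0.855 / 0.955 = 89.5% to 0.72 / 0.82 = 87.8%.

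The dropped column keeps patients who fail the pinch in the denominator. The same criterion also covers a change of method before surgery, so some of them could leave too, which would raise the reported rate further.

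**Step 3: between arms, again assumed.** Take P = 95% in both arms, f = 5% after triple and 15% after double injection.

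- Through surgery: 0.95 × 0.95 = 90.3% against 0.95 × 0.85 = 80.8%, a gap of 9.5 points.
- Reported with failures retained: 95% against 95%, no gap.
- Reported with failures dropped: 94.8% against 0.8075 / 0.8575 = 94.2%, a gap of 0.6 points.

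**The case against.** The strongest case is that this is a design preference. The Discussion gives the aim as block dynamics, meaning sensory-motor blockade and onset times. A blinded test at a fixed time, at the end of the 30-min assessment window and on the area to be operated on, fits that aim, and the definition says openly that the stimulus is simulated. This stands as a reason to keep the pinch test. It does not justify calling the result successful surgical anaesthesia, and it does not answer the lack of any outcome in which an intraoperative failure counts.

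A reader might infer that every block that passes the pinch and fails later is counted as a success. The documents do not support that: a change of anaesthetic method during surgery is a dropout criterion, so converted patients are removed rather than credited. A reader might also infer that a sizeable treatment difference is being hidden. The documents contain no failure rates, so a hidden difference is possible but cannot be shown.

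Two practical objections stand. The Allocation and blinding section lists patients, the outcome evaluator and follow-up personnel as blinded, but not those who decide on intraoperative supplementation, so a through-surgery outcome is more open to judgement than the pinch. Power would also be low. For an assumed 95% against 85% with 43 per arm and two-sided 0.05, the pooled standard error is √(2 × 0.9 × 0.1 / 43) = 0.065 and the unpooled one is √((0.0475 + 0.1275) / 43) = 0.064. Then (0.10 − 1.96 × 0.065) / 0.064 is about −0.4, a power of about one third. The new outcome should be read mainly as an estimate with its interval.

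**Conclusion.** The point holds in this limited form. The definition is explicit, so it is not a matter of detail left to a fuller document. Followed as written, the plan has no place where an intraoperative block failure is scored as one. What the outcome can support is a comparison of painless response to a simulated stimulus at 30 min.

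The conclusion rests on two readings: that the pinch precedes incision, which the wording implies, and that a dropout leaves the analysed set, which is the plain reading but which a fuller protocol or analysis plan might settle differently. The sizes in the illustration are assumptions throughout and say nothing about the likely failure rate in this trial.

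The reach is limited. The outcome is secondary, and neither the definition of the primary outcome (sensory score at 20 min) nor the sample-size calculation uses it. The change is worth making because it is cheap and widens what the trial can conclude.

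**What to change.** These changes concern coding and reporting only; none alters how patients are managed.

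1. Keep the blinded 30-min pinch unchanged, under a name that says what it is, such as simulated-stimulus readiness at 30 min.
2. Add a separate secondary outcome from the anaesthetic record: operation completed without supplementary infiltration, additional block, extra analgesia given for surgical-site pain, or conversion.
3. Reconcile the Dropout criteria with the Secondary outcome measures. A patient whose anaesthetic method changes because the block is inadequate stays in the randomized arm and counts as a failure on the new outcome. A change for an unrelated reason should be recorded as such.
4. Do not split the outcome by operation type. With 43 per arm across about four kinds of operation, roughly 11 each if spread evenly, the cells would be too sparse.

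The cost is about one case-report-form item, a success rate that will look lower, and some judgement by staff not listed as blinded. It also needs an approved amendment: the Trial status section says enrolment had begun, and the Protocol amendments section in principle allows changes only for safety. If an amendment is refused, the minimum is to report intraoperative block failures and dropouts for change of method by arm, and to confine the claim from this outcome to readiness at 30 min.
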